#### Secondary outcomes and data collection methods

Secondary outcomes of Ma Terre-EVAL pilot will include the following variables related to Academia’s behaviours: Number of professional trips by air, percentage of home-to-work trips made by car, by active and sustainable mobility, frequency of numerical equipment purchase, intention towards changing professional trips made by car, reducing home-to-work trips made by car and frequency of numerical equipment purchase equipment [40] and the use of alternatives to air travel through online surveys implemented on the platform Sphinx iQ2 v 7.3.1.0. Moreover, we will collect psychological constructs such as knowledge about climate change (measured through a multiple-choice questionnaire), beliefs about the consequences of behaviour on the climate [9], self-efficacy of choosing an alternative to air travel [40], self-efficacy of choosing an alternative to car travel [40], self-efficacy of making sustainable purchases [40], beliefs about negative consequences of reducing air travel [20], attitudes towards alternatives to air travel [40], attitudes towards alternatives to car travel [40], environmental attitudes [41], ecological identity [42], professional travel habits by air [43], commuting habits by car [43], compensatory beliefs [9], perceived self-control resources [44], descriptive and subjective norms [40] through online surveys. Finally, socio-demographic and institutional information such as gender, age, number of children, self-reported distance between home and work, perceived accessibility by train or alternative transport modes, income levels, career status, employer characteristics, perceived academic recognition and, funding for professional mobility. All the details of the variables, tools and measurement times can be found in Table 2.

### Data management and statistical methods

#### Data quality, management, storage, access and confidentiality

In order to monitor the quality of the data, one member of the scientific team will check the documents filled in by the facilitators (i.e., the documents evaluating the feasibility and the fidelity) and the presence of missing data in these documents after the end of each intervention meeting. This data will be immediately transferred to an Excel table. Furthermore, data from online surveys will be downloaded at the end of each session of measurement.

The data will be stored in two blocks:

Block 1 will contain the contact file including name and email of the participants for sending the surveys and setting the intervention meetings. Moreover, this block will contain the correspondence table between the participants’ identifier and their name. This block will be encrypted and it will only be accessible by the scientific coordinator and the field coordinator.

Block 2 will contain all the collected data from the paper forms and the online surveys. The data will be anonymised (only containing the participant’s identifier).

Both of the blocks will be locally stored on the secured data centre of the university Grenoble-Alpes with access restricted only to Ma Terre-EVAL pilot team.

#### Data monitoring, harms and auditing

No data monitoring committee has been conformed for this study because the researchers have no strong suspicion that any of the interventions can potentially harm the participants. The coordinator of the implementation team and the coordinator of the scientific team will meet once every two weeks to audit the trial conduct.

#### Ancillary and post‑trial care

No ancillary and post-trial care will be provided.

#### Trial registration

Because of the non-clinical character of this research study, we have submitted a registration in https://www.protocols.io/ with the registration number YXMVM24JBG3P.

#### Statistical methods

*Analysis of the feasibility of the intervention and adherence*. Concerning the Task completion, we will identify the tasks that were not completed (i.e., for each group of participants and for each meeting) and we will calculate the percentage of completion of each task (e.g., the discussion about planetary limits was completed in 100% of IM_1_ for experimental and control arms). Concerning the perceived complexity of tasks, we will calculate the average complexity of each task (from 1 to 3) and look at all the comments noted by the facilitators. Concerning the adherence, a participation/absence rate will be done per each intervention meeting.

*Analysis of the feasibility of evaluation*. Concerning the Completion rate of online surveys, we will calculate the percentage of completion of online questionnaires during the first session of measurement (S_0_) and the second session of measurement (S_1_). Concerning the quality of the responses, we will calculate the Median Absolute Deviation [46] to detect outliers that spent too few or too much time to complete the surveys (participants with a Median Absolute Deviation > 3).

*Analysis of the fidelity of the intervention*. Concerning the exposure to the intervention, we will calculate the average duration of each intervention meeting. Concerning the perceived responsiveness of participants, we will calculate the average of perceived responsiveness per each intervention meeting.

## Discussion

Ma-terre EVAL pilot study is a 1-month and a half pilot randomised controlled trial designed to evaluate the feasibility and the fidelity of a 24-month randomised controlled trial aiming to change academic behaviours such as professional mobility by air, daily commuting and digital and material purchases. Ma-terre EVAL pilot study will include a two-arm intervention of 2-weeks: an experimental arm that includes an awareness-raising group discussion, an online carbon footprint assessment and a group session of the serious game “Ma Terre en 180 minutes” [19]; and a control arm which includes only the awareness-raising group discussion and the online carbon footprint assessment. We believe that because the control arm targets mainly raising awareness about climate change and professional behaviours (through the group discussion and the carbon footprint assessment) and consequently it will target sources of behaviour such as capacity and motivation (by using behavioural techniques such as 2.2 self-monitoring of behaviour, 5.3 information about social and environmental consequences, 5.2 salience of consequences according to [31]). Furthermore, the experimental arm will additionally aim the co-construction of ecological transition paths in Academia (through the serious game) and potentially will lead to capacity and opportunity building (by using additional behavioural techniques such as 13.2 framing/reframing, 12.1 restructuring the social environment and 6.2 social comparison according to [31]).

Moreover, the evaluation of the effects of Ma Terre-EVAL pilot study includes two sessions of online surveys to measure the participants’ behaviours (number of professional trips by air, percentage of home-to-work trips made by car and by active and sustainable mobility, frequency of purchasing of equipment), the intention towards changing professional trips made by car, reducing home-to-work trips made by car and frequency of purchasing of equipment, psychological mechanisms related to changing behaviours (attitudes, subjective norms, self-efficacy, ecological identity, habits) and socio-demographic and institutional information (e.g., gender, age, income levels, career status, perceived academic recognition).

Because of the complexity of the interventions proposed to the experimental and control arms and the complexity of the evaluation of the behavioural changes, this pilot randomised controlled trial aims to evaluate the feasibility (the extent to which all the different elements of the interventions and evaluation are feasible for the team implementing the study) of the intervention and the evaluation of the fidelity (the extent to which all the elements of the intervention are accurately implemented and without modifying the behaviour change techniques and contents). Indeed, several authors [39, 47, 48] have indicated that every large-scale study should be pre-tested with small groups of participants to identify elements that could be adapted to ensure better feasibility and fidelity.

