**Methods:**

People employed by a French research organisation (N = 30) will be randomised to one of the two arms. The experimental arm consists in a 1-hour group discussion for raising awareness about climate change, carrying out a carbon footprint assessment and participating to a serious game called “Ma terre en 180 minutes.” The control arm consists of the same intervention (1h discussion + carbon footprint assessment) but without participating to the serious game. On two occasions over one month, participants will be asked to fill in online surveys about their behaviours, psychological constructs related to behaviour change, sociodemographic and institutional information. For every session of intervention, the facilitators will assess task completion, perceived complexity of the tasks and the perceived responsiveness of participants. Descriptive statistics will be done to analyse percentages and averages of the different outcomes.

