**ASSESSMENTS:**						
***Feasibility of the intervention and adherence*** *Task completion*, *Perceived complexity of tasks*, *Participation in sessions*				X	X	
***Feasibility of the evaluation*** *Completion rate of online surveys*, *Quality of responses*			X			X
***Fidelity of the intervention*** *Exposure to the intervention*, *Perceived responsiveness of participants*				X	X	
***Academic’s behaviours*** *Number of professional trips by air*, *Percentage of home-work trips made by car or other modes*, *Frequency of purchasing of equipment*, *Use of alternatives to air travel*				X		
***Psychological constructs*** *Intention towards changing behaviours*, *Knowledge about climate change Beliefs about the consequences of behaviour on the climate*, *Self-efficacy*, *Beliefs about negative consequences of reducing air travel*, *Attitude*, *Environmental attitudes*, *Ecological identity*, *habits*, *Compensatory beliefs*, *Self-control resources*, *Descriptive and subjective norms*			X			X
***Sociodemographic and institutional information*** *Gender*, *age*, *number of children*, *self-reported distance between home and work*, *perceived accessibility by train or alternative transport modes*, *income level*, *Career status*, *employer*, *characteristics*, *academic recognition*, *funding for professional mobility*						

Note. S = Session (Survey to be fill up), SI = Session if intervention.

**Table 2 pone.0301124.t002:** Summary of the variables, tools and time measurements.

Outcomes	Tool	S_0_	SI_1_	SI_2_	S_1_

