**Secondary outcomes**					
**Academic’s behaviours**					
Number of professional trips by air	Survey	✔			
Percentage of home-work trips made by car et by active and sustainable mobility	Survey	✔			
Frequency of purchasing of equipment	Survey	✔			
Intention towards changing professional trips made by car, reducing home-work trips made by car and frequency of purchasing of equipement	Adapted survey [40]	✔			✔
Use of alternatives to air travel	Survey	✔			

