**Fig 2 pone.0301124.g002:**
[figure not shown]
Calendar of Ma Terre-EVAL pilot study and the measurements. S = Session (Survey to be fill up), M = Month, IM1 = Intervention meeting with experimental and control arm. IM2 = Intervention meeting only with experimental arm. Notebook = Online survey.

Approximately two weeks after this session, participants of both experimental and control arm will have the first intervention meeting (IM_1_) with another four participants of their same arm and a facilitator (1 hour). During this meeting, the participants will have a discussion aiming to raise awareness between academic behaviours and environmental issues (all the details of this session will be described in the section “Intervention”). At the end of this meeting, participants of both arms will be asked to evaluate their carbon footprint through the Micmac app (https://avenirclimatique.org/micmac/simulationCarbone.php) and send it to the implementation team.

Approximately two weeks after this first intervention meeting, only the participants of the experimental arm will be contacted to carry out a second intervention meeting (IM_2_) with four participants of their same arm and a facilitator (2 hours and 20 minutes). During this meeting, the participants will participate to the serious game “Ma Terre en 180 minutes” aiming to discuss the possible transition pathways to diminish carbon emissions while playing the role of fictional research laboratory team members (all the details of this session will be described in the section “Experimental Arm”). During and after each of the meetings (IM_1_ and IM_2_) the facilitators will complete a checklist and answer questions about the sessions (see Table 2 and S1–S3 Tables. Tables to be filled up by the facilitators to evaluate de fidelity and feasibility).

Two weeks after the experimental arm’s intervention meeting session (IM2) and one month after the control arm’s intervention meeting session (IM2), the participants will receive a link to complete a 15-minutes online survey (“Session 1” or “S_1_”).

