### Outcomes and data collection

#### Primary outcomes and data collection methods

The main outcomes of Ma Terre-EVAL pilot will be the feasibility of the intervention, the feasibility of the evaluation of behavioural changes and the fidelity of the intervention.

The intervention’s feasibility will be operationalised in three variables: 1) Task completion (a checklist of all activities that need to be carried out during the intervention sessions), 2) Complexity of the intervention tasks (a scale of 1 to 3, from easy to difficult) and 3) Percentage of participation in the meetings (percentage of people absent or present at the intervention meetings). All of this information will be collected through paper questionnaire.

The feasibility of the evaluation of behavioural change will be operationalised in two variables: 1) Completion rate of the online questionnaires (average of the completion of each questionnaire) and 2) Quality of the answers (considering the duration of each questionnaire). More precisely, the quality of the answers will allow us to detect participants who potentially do not take the task seriously enough (i.e., with unrealistic short time on certain tasks) by calculating the Median Absolute Deviation [46] to detect outliers on the time spent on the page showing the article and will exclude participants with a Median Absolute Deviation superior to 3. Both of these outcomes will be calculated by the scientific team by downloading the online surveys completed by the participants of the study.

Finally, the fidelity of the intervention will be operationalised in two variables: 1) Exposure to the intervention (average time of each session) and, 2) Responsiveness of the participants (via a scale of 1 to 7 from not at all responsive to very responsive, this question will be asked to each facilitator). All of this information will be collected through paper forms. All the details of the variables, tools and measurement times can be found in Table 2.

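### The abstract, the Discussion and the two schedule tables disagree on when the target behaviours are measured, and neither table measures them twice

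*Protocol article*

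**What the plan says.** The article gives the timing of the behaviour measures in several places.

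- **Abstract, Methods:** "On two occasions over one month, participants will be asked to fill in online surveys about their behaviours".
- **Discussion:** the evaluation "includes two sessions of online surveys to measure the participants’ behaviours (number of professional trips by air", followed by commuting and purchases.
- **Table 2, behaviour block:** the rows "Number of professional trips by air", "Percentage of home-work trips made by car et by active and sustainable mobility", equipment purchases and use of alternatives to flying are each ticked at S0 only. Intention to change is the one row in the block ticked at both S0 and S1.
- **Table 1 (SPIRIT schedule):** one mark for the whole behaviour block, which ends with "Use of alternatives to air travel". It stands under SI_1, the first intervention meeting.
- **Timeline of the study:** the S0 questionnaire covers professional mobility, commuting and electronic purchases. S1 is a 15-minute online survey whose content is not itemised.

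The sections on primary and secondary outcomes both refer the reader to Table 2 for measurement times. One of the main outcomes is "the feasibility of the evaluation of behavioural changes". It is operationalised as questionnaire completion and response quality judged by duration, and Statistical methods analyses both at S0 and S1.

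On the timing of S1, the Timeline section places it two weeks after IM2 in the experimental arm and, in the control arm, "one month after the control arm’s intervention meeting session (IM2").

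**The concern.** The pilot exists to try out the evaluation planned for the 24-month trial. The Background defines that trial by three practices (professional air travel, car commuting, and digital and material purchases) and bases its sample size on a reduction in car travel. If Table 2 is followed, the S1 survey contains none of these behaviours, although its completion and duration are primary data. It does repeat intention, most psychological constructs, and the sociodemographic and employment items. The pilot would then say nothing about how well participants complete the behaviour items at follow-up, or whether a within-person change can be formed from them.

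A team building the surveys from the abstract, from Table 1 or from Table 2 would also build three different schedules. The control arm's S1 date has a similar defect, because it is tied to a meeting that this arm does not attend.

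**Working it through.** No sample-size or power figure is involved. The check is a cell-by-cell comparison and a count of weeks.

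**Behaviour measures**

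| Source | S0 | SI_1 | S1 |
|---|---|---|---|
| Abstract and Discussion, read plainly | yes | – | yes |
| Timeline text | yes (three practices) | – | not itemised |
| Table 2, air trips | yes | – | no |
| Table 2, commuting share | yes | – | no |
| Table 2, equipment purchases | yes | – | no |
| Table 2, alternatives to flying | yes | – | no |
| Table 2, intention | yes | – | yes |
| Table 1, behaviour block | no | yes | no |

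Behaviours measured at both S0 and S1: Table 2, 0 of 4; Table 1, 0 of 4.

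The SI_1 position in Table 1 is read from extracted table text and should be checked against the published table. A column shift is unlikely, because the Table 1 rows for intervention feasibility, evaluation feasibility and fidelity fall in the same columns as in Table 2. Table 2 and the Timeline text agree on S0, so the SI_1 mark looks like a slip of one cell.

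**What remains computable under Table 2**

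- Completion rate and duration at S0 and at S1: yes.
- Item non-response and floor effects for the behaviour items at S0, in up to 30 participants: yes.
- Completion and quality of the behaviour items at follow-up: no.
- Within-person change in any of the four behaviours: no.

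**Timing of S1** (intervals as stated in the Timeline section, one month taken as about 4 weeks)

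- Experimental arm: S0 to IM1, 2 weeks; IM1 to IM2, 2 weeks; IM2 to S1, 2 weeks. Total 2 + 2 + 2 = 6 weeks.
- Control arm, counted from IM1: 2 + 4 = 6 weeks.

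Both agree with the stated study length of a month and a half.

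**How sparse S1 counts would be.** Study setting cites a survey in which 25% to 35% of respondents flew for work between 2017 and 2019. If the 30 pilot participants resembled them, 30 × 0.25 = 7.5 to 30 × 0.35 = 10.5 would have flown over that whole period, and probably fewer in any six weeks. Commuting recurs throughout the follow-up, so its mode share does not have this problem.

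**The case against.** The strongest defence is that there is no real promise of two behaviour measurements. The Discussion's list for the two surveys also names gender, age, ecological identity and habits, none of which Table 2 repeats at S1, and the abstract's list includes sociodemographic information. Both can be read as the pooled content of two surveys, with Table 2 supplying the timing. Measuring behaviours at S0 only could also be deliberate, since flights and purchases will be rare over six weeks. The section on recruitment, allocation and blinding says that determining effects is not an aim of the pilot.

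Much of this stands. The pooled reading is possible, and no effect estimate is being asked for. But that reading does not reconcile Table 1 with Table 2. Nor does it fill the gap that a main outcome concerns evaluating behavioural change while no behaviour is measured a second time. If six weeks was judged too short, the article does not say so, and the argument is weak for commuting.

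A reader might infer more than the article supports:

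- **That the pilot cannot test the evaluation of behaviour change at all.** The article defines that outcome as completion and response duration, and both are available at S0 and S1.
- **That non-response and floor effects for the behaviour items would stay unknown.** S0 will show them. Only the follow-up versions go untried.
- **That the control arm is surveyed about 8 weeks after S0 (2 + 2 + 4) against 6 in the experimental arm.** That count starts from an IM2 which Table 1, Table 3 and the Fig 2 legend show the control arm does not have. The month-and-a-half duration points to IM1.
- **That the pilot fails to fill the gap in earlier research.** The Background assigns that aim to the Ma Terre-EVAL study, which it describes as the 24-month trial with 1000 participants.

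**Conclusion.** The inconsistency is real. Table 2 gives S0 only, Table 1 gives SI_1 only, and the abstract and Discussion, read plainly, give two surveys. Under either table 0 of 4 target behaviours is measured again, so the feasibility of evaluating behavioural change is incompletely tested. No primary outcome becomes uncomputable, so this should be fixed but is not a fatal defect. The control arm's S1 anchor is a separate labelling error; timed from IM1, S1 falls at about six weeks in both arms.

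This rests on two assumptions: that Table 2 governs, as the outcome sections say, and that the columns of Table 1 were extracted correctly. If the Table 1 mark actually stands at S0, the two tables agree with each other but still provide no follow-up measurement.

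**What to change.** 1. In Table 1, move the behaviour mark from SI_1 to S0.
2. In both tables, add the behaviour items at S1 with a stated recall window. Commuting share is the minimum, because the main trial's sample size rests on car travel and commuting recurs over six weeks. All four would be preferable.
3. If the team prefers to measure behaviours once, say so in the abstract and the Discussion, and state that repeat behaviour measurement is not piloted.
4. Keep the sociodemographic and employment follow-up block. Cutting it to save time would leave other follow-up items untried, including perceived accessibility of alternatives and mobility funding, which can change.
5. In the Timeline section, change the control arm's S1 anchor from IM2 to IM1.

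The cost of option 2 is an S1 survey somewhat longer than the planned 15 minutes, with air-trip and purchase counts that are likely to be sparse. The remaining changes are edits to text and tables. No extra participants or meetings are needed.
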